### Plan for retaining participants

Methods are needed to promote participant retention. First, we will select the coordinator and nurse carefully and train them strictly before the trial begins. Furthermore, we will focus on daily communication and monitoring. The coordinator and nurse should have empathy and good communication skills to gain the patient’s trust to improve patient retention and completion of the follow-up period. In addition, we will provide extra incentives.

### Sample size

A similar clinical trial has been conducted using TCM to decrease the rate of symptoms (fever, fatigue and coughing) in patients with COVID-19 [14]. The rate of recovery of clinical symptoms was 91.2% in patients who received TCM treatment and 61.1% in patients who received conventional treatments. Considering 90% power with a significance level of 10%, as well as a rate of withdrawal and loss to follow-up of 10% [15], we plan to recruit at least 150 participants in each group to achieve sufficient precision in a subsequent full trial.

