### Statistical analysis

We will not conduct subgroup or adjusted analyses of the trial. The independent statistical analysts will be responsible for the data analysis. All patients will be analysed on the basis of intent-to-treat analysis, including all randomized subjects who take Baidu Jieduan granules at least once and have follow-up information recorded. In the case of missing data, multiple imputation will be carried out to generate missing values. A per-protocol analysis, which includes patients who completed the trial without conflict with the major protocol, can be conducted as appropriate. Then, the statistician will submit statistical reports in a timely manner to the study director. The statistical analysis will be performed in a blinded manner using SPSS 20.0 software. Continuous variables characterizing each study group will be expressed as the mean with standard deviation or median with interquartile range. Categorical variables will be reported as frequencies and proportions. Continuous outcomes will be analysed by unpaired Student’s *t*-test or Wilcoxon’s nonparametric statistic, while count data will be compared using a chi-square test or Fisher’s exact test. All statistical tests will be two-sided. *P* < 0.05 will be considered statistically significant. We will not carry out an interim analysis.

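### The stated sample-size inputs give roughly 28 to 44 patients per group, not 150; the 10% planning level contradicts the two-sided 5% test; and the rates used belong to only one of two named primary outcomes.

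*Protocol article*

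**What the plan says.** All inputs are in the Sample size section of the protocol article. From an earlier trial of traditional Chinese medicine it takes two recovery rates: "The rate of recovery of clinical symptoms was 91.2% in patients who received TCM treatment" and "61.1% in patients who received conventional treatments". It then sets the design values, "Considering 90% power with a significance level of 10%, as well as a rate of withdrawal and loss to follow-up of 10" per cent, and concludes: "we plan to recruit at least 150 participants in each group to achieve sufficient precision in a subsequent full trial". It does not say whether the 10% level is one-sided or two-sided.

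The Statistical analysis section fixes a different error rate: "All statistical tests will be two-sided", and a P value "< 0.05 will be considered statistically significant". Count data are to be compared by chi-square or Fisher's exact test.

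The primary outcome is named twice, differently. The abstract (Methods/design) gives the rate of symptom recovery. Outcomes and measurements gives the proportion with a negative SARS-CoV-2 nucleic acid result on day 14 and lists time to symptom recovery as secondary. The article gives no expected rates for nucleic acid negativity.

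**The concern.** A sample-size statement should let a reader get from the inputs to the number. Here the inputs are complete apart from sidedness, yet the number is about four times what they produce. The planning level is also twice the level at which the trial will be tested, and the planning rates belong to an outcome that one section makes primary and another does not.

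What is at stake is what the result can be taken to mean. If the trial finds no significant difference, a reader will ask what difference it was built to detect. The article's answer, 30.1 points with 90% power, is wrong for 150 per group. If nucleic acid negativity is the primary outcome, there is no answer at all. The section also justifies randomising 300 patients on figures that support about 106 at most at the level the trial will use (53 per group, with continuity correction and loss).

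**Working it through.** **Inputs.** From Sample size: p1 = 0.912, p2 = 0.611, difference d = 0.301, power 0.90, significance level 0.10, loss 0.10, 150 per group. From Study design and settings: 1:1 allocation, 300 in total. From Statistical analysis: two-sided tests at 0.05.

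**Formula.** Two proportions, pooled-variance normal approximation, per group:

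n = [z_a √(2 p̄(1−p̄)) + z_b √(p1(1−p1) + p2(1−p2))]² / d²

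Here p̄ = (0.912 + 0.611)/2 = 0.7615, so √(2 × 0.7615 × 0.2385) = 0.6027. The second root is √(0.0803 + 0.2377) = 0.5639, and z_b = 1.2816. The continuity-corrected size, close to what Fisher's exact test needs, is n_c = (n/4)[1 + √(1 + 4/(n d))]². Each n is rounded up, divided by 0.9 for loss, and rounded up again.

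**Attempt to reproduce 150 from the stated inputs.** With 10% taken as two-sided, z_a = 1.6449:

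n = (0.9913 + 0.7226)² / 0.0906 = 32.4, so 33; 33/0.9 = 36.7, so 37.

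With continuity correction: 38.8, so 39; 39/0.9 = 43.3, so 44.

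The other readings follow in the same way:

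| Level | z_a | n per group | after 10% loss | n corrected | after 10% loss |
|---|---|---|---|---|---|
| 10% two-sided | 1.6449 | 33 | 37 | 39 | 44 |
| 10% one-sided | 1.2816 | 25 | 28 | 31 | 35 |
| 5% two-sided (analysis section) | 1.9600 | 41 | 46 | 47 | 53 |

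Unpooled-variance and arcsine formulas give 31 at two-sided 10% and 24 at one-sided 10%, before loss. The strictest combination tried (two-sided 1%, 99% power, continuity correction, 10% loss) gives 109. None reaches 150. Against the stated inputs, 150 is between 150/44 = 3.4 and 150/28 = 5.4 times the derived size.

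**How much the conflict of levels explains.** Moving from two-sided 10% to two-sided 5% raises the size from 37 to 46 per group. It is a separate defect and does not account for 150.

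**Power at the planned size.** 150 × 0.9 = 135 evaluable per group. At two-sided 5%:

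(0.301 × √135 − 1.9600 × 0.6027) / 0.5639 = 4.11, so power is Φ(4.11) = 0.99998.

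At two-sided 10% the argument is 4.44 and power is 0.999996. Neither is 90%.

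**What 135 evaluable per group detects.** Solving the same formula for p1 with n = 135, two-sided 5% and 90% power:

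| Control rate | Source | Difference (points) | with continuity correction |
|---|---|---|---|
| 61.1% | Sample size section, symptom recovery | 17.9 | 18.6 |
| 70% | assumed | 16.2 | 16.8 |
| 75% | assumed | 14.9 | 15.5 |
| 80% | assumed | 13.3 | 13.9 |

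The last three rows are for nucleic acid negativity. Their control rates are assumptions, because the article gives none.

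**The case against.** The strongest defence is that the error is on the safe side. The article presents 150 as a minimum and mentions precision, so the sponsor may have wanted a larger trial for a smaller effect, for safety or for secondary outcomes. The analysis level is clear where it matters, in the Statistical analysis section, and nothing suggested here changes enrolment or a test.

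Part of this stands. For the quoted rates the trial is larger than needed, and a floor may be set on other grounds. But the section offers 150 as the consequence of the listed inputs and names no other ground, so the statement remains wrong as written. An analysis plan that is not shown could add a rationale, but it could not make 10% and 5% agree or make these inputs yield 150.

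A reader might infer that planning at 10% and testing at 5% leaves the trial short of power. That would hold for a design sized to exactly 90% power at two-sided 10%: it would have Φ(1.645 + 1.282 − 1.960) = 0.83 at 5%. Such a trial has about 33 evaluable patients per group. This one has about 135, and its power for the quoted rates stays above 99.99%, so the documents do not support that reading.

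A reader might also infer that this is a pilot, because the number is said to serve a subsequent full trial. Nothing else in the article calls it one. The abstract's discussion says it will provide high-quality evidence of efficacy, and it is tested at P < 0.05. The phrase needs an explanation or a correction; the sponsor's intent cannot be read from it.

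**Conclusion.** The point holds, as a misstated justification and not as a shortage of patients. The stated inputs give 37 per group after loss if two-sided (44 corrected) or 28 (35) if one-sided, against 150 stated. The 10% level contradicts the two-sided 5% of the analysis, and nothing else in the article reconciles the two. For 91.2% against 61.1%, the planned size has over 99.99% power, so 90% describes neither level.

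The power statement concerns symptom recovery only. If day-14 nucleic acid negativity is the primary outcome, its power is unknown from this article; it has not been shown to be inadequate.

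The figures rest on a normal approximation, on the quoted rates being the planning rates, and on 10% loss in each group. The mismatch with 150 does not depend on sidedness, continuity correction or the choice among the three formulas tried.

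**What to change.** Keep 300 patients and rewrite the justification:

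1. State a two-sided 5% level in both Sample size and Statistical analysis.
2. Choose one primary outcome and make the abstract and Outcomes and measurements agree. The power sentence cannot be finalised before this.
3. Replace the present claim with the difference detectable with 90% power from 150 randomised and 135 evaluable per group. For symptom recovery with 61.1% in control, that is about 17.9 points (18.6 with continuity correction). For nucleic acid negativity, give the control rate expected and its source; for assumed rates of 70%, 75% or 80% the differences are 16.2, 14.9 or 13.3 points (16.8, 15.5 or 13.9 corrected). Quote the corrected figures if Fisher's exact test may be used.
4. If 150 was chosen on other grounds, say which.
5. Correct or explain the reference to a subsequent full trial.

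The cost is text only. The stated power claim changes; enrolment and the 5% test do not.

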### Randomization and blinding

The enrolled participants will be randomly assigned to the Baidu Jieduan granule group or the conventional treatment group according to random codes. The random sequence of 300 participants from 4 medical centres will be generated by SPSS 19.0 and stratified by centre. Two sets of random codes will be stored in opaque envelopes, which will be sent to the research sponsor and each of the centres. Thereafter, the drug administrators will arrange the nurse to dispense the study drug in the order of random numbers. This will be an open-label study. The statistical analysis will be carried out by the Professors of Statistics of Shanghai University of Traditional Chinese Medicine, who will be blinded to the patient allocation.

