## Methods/design

### Study design and settings

The study is designed as a randomized, placebo-controlled, multicentre trial, which will be conducted at four medical centres selected by the expert committee: the Huangshi Hospital of Traditional Chinese Medicine; Tongji Hospital, Tongji Medical College, Huazhong University of Science and Technology; LaoHeKou Traditional Chinese Medicine Hospital; and Leishenshan Hospital of Wuhan. A total of 300 participants fulfilling the eligibility criteria will be randomized into two groups (Baidu Jieduan granule group and control group) at a ratio of 1:1. The study flowchart is illustrated in Fig. 1. The Standard Protocol Items Recommendations for Interventional Trials (SPIRIT) checklist is presented in Additional file 1.

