### Interventions

The Baidu Jieduan granules are composed of 15 g of *Rheum palmatum L.* stem (*Dahuang*), 30 g of *Sargentodoxa cuneata (Oliv.) Rehd. et Wils.* (*Hongteng*), 30 g of *Taraxacum mongolicumHand.-Mazz.* (*Pugongying*), 45 g of *Raw Gypsum* (*Sheng Shigao*), 9 g of Herba Ephedra (*Mahuang*), 45 g of *Talcum* (*Huashi*), 12 g of *Amygdalus Communis Vas* (*Xingren*), 9 g of *Radix Glycyrrhizae (Gancao)*, 30 g of *Verbena officinalis L.* (*Mabiancao*), 30 g of *Polygonum cuspidatum* (*Huzhang*), 30 g of *Scutellariae Radix* (*Huangqin*) and 12 g of *Bombyx batryticatus* (Jiangchan), packaged in two bags. The Baidu Jieduan granules will be administered orally two times a day for 14 days. The Baidu Jieduan granules are manufactured by Beijing Tcmages Pharmaceutical Co., Ltd. (number: Jing 20180032).

The participants will be categorized into two groups receiving either standard Western medicine alone according to the *Protocol for Diagnosis and Treatment of Novel Coronavirus Pneumonia* (7th edition) or the combination of Baidu Jieduan granules two times a day for 14 days plus standard care. Routine care includes early fluid resuscitation, antimicrobial anticoagulants, nutritional support and other treatments. Other TCM therapies, including TCM injections and other oral herbal medicines, will be prohibited.

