### Outcomes and measurements

The primary outcome will be the proportion of negative SARS-CoV-2 nucleic acid results on the 14th day. The secondary outcomes will be the time to symptom recovery, the proportion of cases with reversion on chest CT, the time to negative SARS-CoV-2 nucleic acid results and the proportion of participants regrouped as severe cases. Symptom recovery is defined as the complete disappearance of fever, fatigue and coughing symptoms.

Evaluation of the primary and secondary outcomes will occur at five points (before treatment and the 3rd, 5th, 7th and 14th days of hospitalization).

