## Discussion

The high transmission efficiency of COVID-19 has had a significantly negative impact on the global economy and community [17]. COVID-19 can cause lung inflammation and infiltration, with inflammatory cytokine storms induced by SARS-CoV-2 infection [17]. The current management strategy mainly relies on supportive therapies. Other agents, including lopinavir (LPV)-ritonavir, remdesivir, chloroquine/hydroxychloroquine and favipiravir, have been assessed in clinical trials [18]. TCM was first documented approximately 2500 years ago and then popularized by globalization. Chinese medicine has prominent value and extensive applications in the treatment of COVID-19, since no other agents have been proven to be effective [7, 19]. Additionally, TCM possesses the advantages of being simple, convenient, efficient and inexpensive with fewer side effects.

Baidu Jieduan granules, as an experiential prescription for the treatment of COVID-19, evolved from Maxing Shigan decoction and our experiential prescription, Jinhong decoction, with the addition of *Verbena officinalis L.* (*Mabiancao*), *Polygonum cuspidatum* (*Huzhang*), *Scutellariae Radix* (*Huangqin*) and *Bombyx batryticatus* (Jiangchan). *Verbena officinalis L.* and *Polygonum cuspidatum* have the effects of expelling wind and removing dampness, clearing heat and detoxifying the body, invigorating the circulation of blood, relieving cough and reducing sputum production [20, 21]. *Bombyx batryticatus* can eliminate external wind, resolve phlegm, dissipate nodules, clear heat and dissipate stagnant heat [22]. *Scutellariae Radix* can clear heat patterns, especially of the upper Jiao, dry dampness and eliminate toxicity [23]. Traditional medicine theories serve as a powerful guide in prescribing Chinese herbal formulas.

This trial is a well-designed, multicentre open-label RCT from the perspective of evidence-based medicine to assess the efficacy and safety of Baidu Jieduan granules in the management of COVID-19 for the first time. The trial can provide a clinical basis for adopting the “San Tong” and “Truncation and Reversion” strategies in the prevention and treatment of patients with COVID-19 and further enrich the theory and practice of treating infectious diseases with TCM. Nevertheless, the design of the trial also has potential limitations. It is not a double-blind, placebo-controlled clinical trial.

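### Only the statisticians are stated as blinded in this open-label trial; no masking is stated for classifying chest CT reversion, a reader-dependent secondary outcome

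*Protocol article*

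**What the plan says.** The Randomization and blinding section of the protocol article states "This will be an open-label study". It then says that statisticians at a named university will do the analysis, "who will be blinded to the patient allocation". The Statistical analysis section returns to blinding once: "The statistical analysis will be performed in a blinded manner using SPSS 20.0 software". No other role is described as masked anywhere in the article.

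The Interventions section gives the control arm as "receiving either standard Western medicine alone", so there is no dummy product. The Discussion concedes the limitation: "It is not a double-blind, placebo-controlled clinical trial".

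The Outcomes and measurements section includes among the secondary outcomes "the proportion of cases with reversion on chest CT" and "the proportion of participants regrouped as severe cases". It defines symptom recovery. For CT reversion and for regrouping as severe it gives no criterion, no assessor and no statement on masking. The primary outcome in that section is nucleic acid negativity at day 14.

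**The concern.** An open-label design fixes what patients and ward staff know. It does not fix what the person classifying a scan knows: a CT image does not show the treatment arm, so the reading can be masked in a trial without placebo. The article has a section devoted to blinding, and that section stops at the analyst.

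Masking the analyst protects choices made during analysis. It does nothing for a call that was already tilted when it was recorded. A reader who knows that a patient takes the granules may more readily call a borderline scan improved. A clinician who knows it may more readily leave a borderline patient in the less severe class. Both errors favour the granules, on outcomes that are meant to support the primary one.

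**Working it through.** **Step 1. Who is masked.**

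| Role | What the article states |
|---|---|
| Patients, ward staff | Open-label (Randomization and blinding; conceded in the Discussion) |
| Statisticians | Blinded (Randomization and blinding; Statistical analysis) |
| CT reader | Not identified; masking not stated |
| Person regrouping as severe | Not identified; masking not stated |

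The random codes go to each centre and a nurse dispenses the granules, so allocation is known on the wards. Whether it reaches the radiology department is not stated.

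The Study design and settings section carries a contrary label: "The study is designed as a randomized, placebo-controlled, multicentre trial". It cannot be used to infer masking, because the sections on blinding and interventions and the Discussion all contradict it. The label should be reconciled with them.

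**Step 2. Possible size of the bias (illustration, all inputs assumed).** Suppose there is no true difference and a fraction b of scans is borderline. With known allocation, a borderline scan is called favourable with probability g in the granule arm and c in the control arm. Then

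spurious difference = b × (g − c)

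- b = 0.20, g = 0.60, c = 0.40: 0.20 × 0.20 = 0.04, or 4 points.
- b = 0.30, g = 0.65, c = 0.35: 0.30 × 0.30 = 0.09, or 9 points.

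Sample size does not enter the formula, so recruiting more patients does not reduce the bias.

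**Step 3. Effect on a two-sided 5% test (also an illustration).** The sample size is from the article: 150 per group less 10% loss, 150 × 0.90 = 135 per arm. Assumed: a true reversion rate p of 50% to 70% in both arms, and a shift d placed wholly in the granule arm. With the normal approximation, the upper-tail rejection probability is

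Φ[(d − 1.96 × SE0) / SE1],

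where SE0 uses the pooled proportion and SE1 the two separate ones. The lower tail is added with −d in place of d.

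For p = 0.60 and d = 0.05:
- SE0 = √(0.625 × 0.375 × 2/135) = 0.0589
- SE1 = √((0.60 × 0.40 + 0.65 × 0.35)/135) = 0.0588
- upper tail = Φ[(0.05 − 0.1155)/0.0588] = 0.133; with the lower tail, 0.135

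| True rate p | 5-point shift | 10-point shift |
|---|---|---|
| 50% | 0.130 | 0.378 |
| 60% | 0.135 | 0.406 |
| 70% | 0.151 | 0.475 |

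A nominal 5% error rate would become about 13% to 15% with a 5-point shift and about 38% to 48% with a 10-point shift. Nearly all of these false positives would favour the granules.

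**Step 4. What the fix changes.** It leaves sample size, power and significance level untouched.

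**The case against.** The strongest reply is that the article never says who reads the scans or classifies severity. It is a condensed account, and reading procedures may stand in the full protocol. This stands in part. A reader might infer that CT reversion and regrouping are judged by staff who know the arm. That is plausible, since allocation is open at the sites, but no section states it, and an open-label trial can have radiologists who do not know the arm. What remains is that a section written to say who is blinded names only the analysts. If a masked reader is already planned, one sentence settles the point.

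A second reply is that masking is not free. This also stands. Leaving the arm off a request form does not stop a site radiologist from opening the ward record, and the article does not describe what the request or case report form shows. Stricter masking would probably need de-identified scans and a reader outside the treating site. The modest version reduces the bias without abolishing it.

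Third, regrouping as severe may rest on objective values, which would leave less room for bias. The article cites a national diagnosis and treatment guideline but reproduces no severity criteria, so this cannot be judged from the document. Study coordinators would be unsuitable as masked assessors here: the article gives them daily communication with patients, a part in recruitment and consent, and a part in evaluating adverse events.

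Fourth, symptom recovery, which the Abstract names as primary and which supplies the planning rates, is more exposed than a scan. That is true, but patients know their arm, so masking an assessor helps less there. CT is where masking is practical.

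Finally, the open-label limitation is disclosed. Disclosing the absence of placebo does not explain why outcome reading should be left unmasked.

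**Conclusion.** The point holds in a limited form and is worth correcting. The plan names only the analysts as blinded, and it states no masking for a reader-dependent secondary outcome that could be read without knowledge of the arm. The same gap applies to regrouping as severe.

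The size is not known. The 4 to 9 points, and the error rates that go with shifts of similar size, rest wholly on assumed borderline fractions, reader shifts and reversion rates. They show that the bias could matter, not that it will occur, and no figure is available for regrouping.

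A reader might go further and conclude that the trial's main result is compromised. The document does not support that. The primary outcome in the Outcomes section is a laboratory result, less open to this bias, and both outcomes discussed here are secondary.

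**What to change.** Add to the Randomization and blinding section that baseline and follow-up chest CTs are classified for the trial by the radiologist who already reports them, that the treatment arm is withheld from the request and the reading form, and that the call is recorded before any contact with the ward.

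For regrouping as severe, state that classification is made from recorded values against criteria fixed in advance. It should be done by existing staff who take no part in that patient's care, consent or adverse event review and who are not shown the arm. Which criteria apply is for the sponsor to specify.

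The cost is wording and a small administrative effort to keep the arm off the forms. No extra scan or reader is needed, and the open-label design and treatments are unchanged. The remaining weakness is that masking fails if the reader opens the ward record; the article should say so.
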